## 3. Stability observation period

Infants with successful withdrawal of oxygen and respiratory support should be observed for 30 min using an SpO2 monitor and a respiratory heart rate monitor.

CI or SI should record occurrences of cardiopulmonary events and major cardiopulmonary events during the three evaluation periods using the SORT record forms.

- cardiopulmonary events

- i. Sustained SpO2 <90% (<5 min)
- ii. Bradycardia (pulse <80 beats/min) (≥10 sec)
- iii. Apnea (breathing cessation ≥15 sec)

- Major cardiorespiratory events

- i. ≥3 consecutive apneas or bradycardia in a 5-min period or during the test period
- ii. SpO2 <80% for ≥15 sec
- iii. SpO2 <70% requiring stimulation to recover

CI or SI should judge SORT as a success if the infant does not show any major cardiorespiratory events, maintaining SpO2 at 90% or higher in room air during the stability observation period. On the contrary, CI or SI should judge SORT as a failure in the following two conditions (i or ii):

- i. If major cardiopulmonary events occur during the oxygen/pressure reduction and stability observation period
- ii. If one of the cardiopulmonary events occurs during the oxygen/pressure reduction and stability observation periods, and the attending physicians decide that SORT should not be continued.

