## 4.3 REASONS OF SCIENTIFIC RATIONALITY

In Japan, AZM and EM have not been approved for the treatment of pPROM, and clinical trials have not been conducted. Therefore, we decided to conduct a phase II, multicenter, open-label, randomized, parallel-group, open-label study to explore and compare the efficacy and safety of

AZM and EM as prophylaxis against BPD in infants born to pregnant women with pPROM occurring at <28 weeks of gestation.

In this study, referring to previous studies, the target population was defined as pregnant women with singleton pregnancies who developed pPROM from 22 weeks 0 days to 27 weeks 6 days gestation. The earlier the gestational week of pPROM onset, the BPD incidence rate is higher. Therefore, weeks of gestational age at onset of pPROM will be used as a stratification factor for randomization.

The primary outcome of this study was the incidence of moderate or higher BPD36 or infant death by 36 weeks PMA. BPD is a lung tissue disorder that develops due to prematurity, prolonged ventilator management, high concentrations of oxygen, infection, etc. It occurs mainly in preterm infants and requires long-term oxygen administration and respiratory support (e.g., ventilator with tracheal intubation, nasal continuous positive airway pressure [NCPAP], high-flow nasal cannula [HFNC]).

Most BPD definitions proposed in recent years use the presence or absence of oxygen and respiratory support. In addition, the current classification of severity using oxygen and respiratory support use at 36 weeks PMA is the classification reported by NICHD in 2001, which is widely used both inside and outside the country. Therefore, for this study, BPD36 occurrence is defined as "presence or absence of oxygen or respiratory support use at 36 weeks PMA (for children born at 32 or more weeks of gestation at birth, presence or absence of oxygen or respiratory support use at days 28 to 56 or discharge home, whichever occurs first)" and BPD severity classification uses "NICHD, 2001". If the patient is using between 22% and 30% oxygen at the time of assessment, the supplement oxygen reduction test (SORT) is used to diagnose BPD.

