| Severe BPD | Requires oxygen or positive pressure ventilation (artificial ventilation or NCPAP) of at least 30% at 36 weeks 0 days PMA or discharge, whichever comes first | Requires oxygen or positive pressure ventilation (artificial ventilation or NCPAP) of at least 30% at day 56 or discharge, whichever comes first |
|------------|---------------------------------------------------------------------------------------------------------------------------------------------------------------|--------------------------------------------------------------------------------------------------------------------------------------------------|

At the time of evaluation, the respiratory status should be assessed and an supplement oxygen reduction test (SORT)\*1 should be performed to determine BPD severity in children who have any ((8) through (11)) of the following (1) through (14). Upper respiratory tract disease is excluded.

- ① Non-intubated positive pressure ventilation with artificial ventilation NIPPV and NIV-NAVA by tracheal intubation
- ② More than 30% oxygen administered by mask.
- ③ Positive pressure ventilation (\*) in non-intubated use and receiving at least 30% oxygen
- ④ Nasal cannula using more than 100% oxygen 251 mL/min
- ⑤ Discharged on oxygen only (FiO2 0.30 or higher)
- ⑥ Discharged on oxygen only (FiO2 less than 0.30)
- ⑦ He/she was discharged from the hospital with a ventilator.
- ⑧ Oxygen less than 29% and positive pressure ventilation under nonintubated conditions (including high flow, biPAP, and CPAP)
- ⑨ Oxygen use below FiO2 0.30 in hood or nasal cannula
- ⑩ Nasal cannula with 100% oxygen at 250 mL/min or less
- ⑪ Failure to maintain SpO2 91% or greater on indoor air at 36 weeks 0 days PMA even with oxygen or respiratory assistance on 14 consecutive days prior to 36 weeks 0 days PMA
- ⑫ Oxygen administration period is less than 28 days
- ⑬ SpO2 of 91% or greater for at least 14 days without any respiratory support or oxygenation
- ⑭ Discharged home without respiratory support or oxygen.

Time of implementation: 36 weeks 0 days (±2 days) PMA, except for children born at 32 or more weeks of gestation, at day 56 or at discharge from the hospital, whichever occurs first. If the patient is unable to perform the SORT due to surgery or other reasons, the SORT should be performed when it is determined that the effects of the surgery or other reason are no longer present.

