## 2. Oxygen/pressure reduction period

If the infant is stable for 15 min during the baseline evaluation period (if SpO2 is maintained at 90% or higher), CI or SI should gradually reduce oxygen, pressure, or flow as follows:

- Pressure for CPAP/directional positive airway pressure (DPAP)/biPAP

The pressure should be gradually reduced to 5 mmHg (about 4 cmH2O) by 1 mmHg (about 1 cmH2O) every 5 min. Then, CI or SI should lower the oxygen concentration to room air and stop respiratory support.

- Oxygen

The oxygen dose should be reduced by up to 100 mL/min every 5 min until an infant with nasal oxygen breathes room air. If an infant is oxygenated with a hood or mask, FiO2 should be reduced by up to 0.10.

- High-flow nasal cannula (HFNC)

CI or SI should reduce the flow rate by 1 L/min every 5 min to 3 L/min, and then discontinue HFNC.

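### The oxygen reduction test (SORT), which can settle BPD severity for infants on low-level support, has a gap in its pass/fail rule, a wrong pressure conversion and oxygen limits that differ between sections

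*Protocol*

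**What the plan says.** The primary outcome counts moderate or severe BPD36 together with fetal and infant death (Protocol sections 1.1 and 3). Section 7.5.3 (6) lists 14 respiratory states at assessment and requires SORT for items 8 to 11.

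- **Pass/fail** (7.5.3 (6), stability observation period): "CI or SI should judge SORT as a success if the infant does not show any major cardiorespiratory events" and holds SpO2 at 90% or higher in room air during that period. Failure has two routes, both covering the reduction and stability periods. One is a major event. The other is a listed cardiopulmonary event "and the attending physicians decide that SORT should not be continued". The desaturation entry among the listed events carries a duration of less than 5 minutes.
- **Pressure** (reduction period): "The pressure should be gradually reduced to 5 mmHg", which the bracket after it gives as about 4 cmH2O. The steps are 1 mmHg, given as about 1 cmH2O.
- **Oxygen limits**: section 4.3 applies SORT "If the patient is using between 22% and 30% oxygen at the time of assessment". Table 7.5-3 puts oxygen below 30% in moderate and 30% or more in severe. Item 3, outside the SORT group, is non-intubated positive pressure "and receiving at least 30% oxygen". Item 8, inside it, is "Oxygen less than 29% and positive pressure ventilation under nonintubated conditions".
- **Who judges**: the site investigator judges SORT, and treatment is open-label (4.1). Section 16.6 gives the final BPD diagnosis and severity to three outside experts blinded to the arm, with details in separate procedures.

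**The concern.** SORT is the step at which an infant on low oxygen, CPAP or high flow can be kept in or taken out of the moderate/severe group. A rule that leaves results unclassified, or that gives different answers in different sections, will be completed differently from site to site, and that adds misclassification to the primary outcome. One failure route also turns on a decision by staff who are not blinded. The blinded-endpoint design is meant to keep such influence out of the diagnosis. The event rates observed here will also be used to size the phase III trial, so errors in them would carry forward.

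**Working it through.** **1. Do the pass/fail conditions cover every result?** Four results set against the written rules:

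- SpO2 85% for 3 minutes during stability observation, test continued, no major event. Not a success, because 90% was not held. Not a failure, because there was no major event and no decision to stop. Unclassified.
- SpO2 82% for 10 minutes during stability observation. Not a success. Not a listed cardiopulmonary event, because the entry covers only less than 5 minutes. Not a major event, because the lowest value is not below 80%. It meets neither failure route, even if the test is stopped.
- One bradycardia during step-down, test stopped by the physicians. Failure.
- The same bradycardia, test continued, infant then stable at 90% or more with no major event. Success.

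The first two show the gap. The last two show the same early event ending in opposite verdicts because of the decision to stop.

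**2. Pressure.** 1 mmHg = 1.3595 cmH2O.

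- 5 mmHg × 1.3595 = 6.80 cmH2O.
- 4 cmH2O ÷ 1.3595 = 2.94 mmHg.

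The stated pair differs by 6.80 − 4 = 2.8 cmH2O. Treating 1 mmHg as about 1 cmH2O, as the step size does, does not give 4 for 5 either. An infant on CPAP of 5 to 6 cmH2O is already below 6.8, so has no pressure step under one reading and one or two under the other.

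**3. Oxygen limits, side by side.**

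- Non-intubated positive pressure, 29% to just under 30%: SORT under 4.3; in neither item 3 nor item 8.
- Non-intubated positive pressure, exactly 30%: SORT under 4.3; item 3 (no SORT) in the list; severe in Table 7.5-3.
- Mask, 22% to 30%: SORT under 4.3; in no item, because item 2 is above 30% by mask and item 9 names only hood and nasal cannula. The reduction procedure nevertheless describes weaning from a mask.

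**4. Size.** Inputs: 50 per arm (5.2.1), control 60%, intervention 18% to 40%, two-sided 5% (5.2.2).

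- The plan's power first, pooled normal approximation. At 60% vs 40%: (0.20 − 1.96 × √(2 × 0.5 × 0.5/50)) ÷ √(0.24/50 + 0.24/50) = (0.20 − 0.196) ÷ 0.0980 = 0.041, so power is 0.516. At 60% vs 18% it is 0.995. Both match the protocol.
- One infant is 1/50 = 2 percentage points. The planned differences are 60 − 40 = 20 to 60 − 18 = 42 points.
- Illustration by assumption only, non-differential error averaged over the whole arm: sensitivity = specificity = 0.95 turns 60% and 40% into 59% and 41%, and power falls from 0.516 to 0.435. At 0.90 the rates are 58% and 42%, and power is 0.358.
- Illustration by assumption only, one-directional error: both true rates 60%, and an expected 1, 2, 3 or 5 of 50 infants in one arm moved from event to non-event. The exact rejection rate of the pooled test rises from 0.052 to 0.058, 0.074, 0.100 or 0.184.

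**The case against.** Several limits on this point are fair and stand.

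- SORT does not decide the primary event in general. Deaths, stillbirths, intubated infants, infants clearly above the oxygen limits and infants off support are classified without it.
- A reader might infer that any fall below 90% with the test continued is unclassified. It is not. Success asks for 90% only during stability observation, so an infant who dips during step-down and then stays stable can pass.
- A reader might infer that 29% oxygen on positive pressure has no rule at all. Section 4.3 supplies one; it is the item list that omits this setting. The moderate/severe boundary is also harmless in itself, since both grades count as events. What matters is whether the infant is tested.
- A reader might infer that the committee sees only the site's verdict. Nothing says so. Events in all three periods go on SORT record forms, and the committee's separate procedures may have it read them.
- Under either pressure figure the infant then goes to room air, support is stopped and 30 minutes of observation follow. The error changes the number of steps, not the end state, and it applies to both arms.

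The three conflicts remain in the text that sites follow. Even a committee that re-reads the forms cannot recover how a test stopped by the site would have ended.

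**Conclusion.** The rules for SORT contradict themselves in the three places shown and should be corrected. The pressure mismatch is arithmetic, and the other two follow from reading the provisions together. The point concerns infants in items 8 to 11 and those at the disputed 29% to 30% and mask settings. It assumes that a passed test keeps an infant from counting as moderate or severe, which is the natural reading of using SORT to determine severity.

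The certain size is 2 percentage points per reclassified infant in an arm of 50, against planned differences of 20 to 42 points. The documents give neither a SORT error rate nor the share of infants who will need the test, so the power losses and false-positive rates above are illustrations, not estimates. They do not show that the result will be biased. The defensible statement is that the protocol leaves room for an arm-dependent decision and does not say whether the blinded committee closes it. No sample size or power figure is wrong.

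**What to change.** Reconcile section 4.3, Table 7.5-3, the item list and the SORT procedure in 7.5.3 (6) so that:

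- each combination of oxygen level, device and support falls under one rule;
- the pressure target has one value, with the two units agreeing;
- each recorded SORT result maps to exactly one verdict by recorded criteria, including desaturation of any duration.

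The sponsor's clinical experts should choose the values and criteria. Declaring every stopped test a failure is a tempting shortcut, but it would be a clinical rule and is not proposed here. It would also sit badly with the existing provisions to defer SORT after surgery and to repeat it after an unstable baseline, with which the chosen criteria must agree.

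In section 16.6, state that the blinded committee assigns the SORT result from the existing record forms without seeing the site's verdict. The same reading can be applied to tests already done.

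The cost is wording in these sections and the committee procedures, and a little more committee work. No new data are needed.

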## (7) Complications in children

Investigate for IVH, PVL, RDS, fetal aspiration syndrome, neonatal transient hypercapnia, prolonged pulmonary hypertension, sepsis, NEC, localized bowel perforation, symptomatic patent ductus arteriosus (PDA), subglottic stenosis, laryngomalacia, upper respiratory tract disease (other).

For IVH, severity (3rd and 4th degree) and diagnostic methods will also be investigated.

For PVL, the site (unilateral or bilateral) and diagnostic methods will also be investigated.

The diagnostic criteria for each complication are defined separately.

Time of implementation: at the end of pregnancy (at birth, day 3, day 7, day 28\*1, 36 weeks 0 days PMA\*2, at discharge of the child)

\*1: For children discharged by day 28, evaluation is performed at the 1-month check-up.

\*2: For children born at 32 or more weeks of gestation, evaluate at day 56 or at discharge from the hospital, whichever comes first.

#### (8) Treatment details for children

Intravenous (duration of administration, daily dose) and inhaled (whether used or not), inhaled nitric oxide (whether used or not), surfactant (whether used or not), caffeine (duration of administration, daily dose), and azithromycin administration (whether used or not) steroids for neonates will be surveyed and entered into the eCRF. In addition, the name of the procedure, date of surgery, purpose of surgery, and whether the child was intubated for the purpose of surgery will be surveyed and entered into the eCRF.

Time of implementation: at the end of pregnancy (at birth, day 3, day 7, day 28\*1, 36 weeks 0 days PMA\*2, at discharge of the child)

\*1: For children discharged by day 28, evaluation is performed at the 1-month check-up.

\*2: For children born at 32 or more weeks of gestation, evaluate at day 56 or at discharge from the hospital, whichever comes first.

### 7.5.4 TEST ITEMS AND TIMING IN THE CHILDREN

#### (1) Umbilical cord artery blood gas

Umbilical artery blood gas (pH) is measured.

Time of implementation: At the end of pregnancy (at birth)

#### (2) blood gas test

Blood gas (pH) measurement. arterial, venous, or capillary blood can be measured.

Time of implementation: at the end of pregnancy (at birth), day 3\*1

\*1: If birth weight is less than 1000 g, no measurement is required.

#### (3) Hematological examination

Hematological tests shall be able to measure arterial, venous, or capillary blood.

Test items: WBC, RBC, Hb concentration, Ht value, PLT

Time of implementation: at the end of pregnancy (at birth)\*1, day 3\*2

\*1: At the end of pregnancy (at birth), cord blood may be used for measurement.

\*2: If birth weight is less than 1000 g, no measurement is required.

#### (4) Blood Biochemical Tests

Blood biochemical tests shall be able to measure arterial blood, venous blood, or capillary blood.

Tests: blood glucose, T-Bil, AST, ALT LDH, CK, Na K, Cl, CRP, IgM\*1

Time of implementation: at the end of pregnancy (at birth)\*2, day 3\*3

\*1: IgM is measured only at the end of pregnancy (at birth).

\*2: At the time of termination of pregnancy, measurement with cord blood is also acceptable.

\*3: If birth weight is less than 1000 g, no measurement is required.

#### (5) Pharyngeal and auricular ureaplasma cultures (central measurement)

If the subject (mother) is found to have novel coronavirus infection, the specimen will not be collected.

Date of implementation: Termination of pregnancy (at birth)

(6) Pharyngeal and auricular Ureaplasma PCR (central measurement)

If the subject (mother) is found to have novel coronavirus infection, the specimen will not be collected.

Time of implementation: At the end of pregnancy (at birth)

(7) chest X-ray

Chest X-rays are evaluated for diffuse opacities, diffuse foamy shadows, and irregular cord-like emphysema-like shadows, which are reported on the eCRF.

Time of implementation: at termination of pregnancy (at birth), day 7\*1, day 28\*2, 36 weeks 0 days PMA\*1,\*3

\*1: When deemed necessary.

\*2: For children discharged by day 28, evaluation is performed at the 1-month check-up.

\*3: For children born at 32 or more weeks of gestation, evaluate at day 56 or at discharge from the hospital, whichever occurs first.

#### 7.5.5 HANDLING OF CENTRALLY MEASURED SPECIMENS

Samples of PCR (vaginal ureaplasma PCR, placental ureaplasma PCR, ureaplasma PCR of the pharynx and ear cavity of the infant, and optional amniotic fluid ureaplasma PCR) which will be measured in central laboratory unit are stored in a refrigerator, and samples of culture (vaginal ureaplasma culture, placental ureaplasma culture, ureaplasma culture of the pharynx and ear cavity of the infant, and optional amniotic fluid ureaplasma culture) which will be also measured in central laboratory unit are stored overnight in a refrigerator at (1) 37 degrees Celsius if possible, (2) room temperature (15-25 degrees Celsius) if no culture device is available, or (3) overnight in a refrigerator and stored at -70 to -80 degrees Celsius on the following day. If stored in a refrigerator, they can be stored for several days. Freezing at -70 to -80 degrees Celsius is possible for several months, and the samples should be kept frozen until the day of delivery service for the samples.

The centrally measured specimens should be sent together at room temperature within two months after the child's specimen collection to the "Department of Developmental Medicine, Research Institute, Osaka Women's and Children's Hospital" by delivery service in Category B. As an option, facilities that perform amniocentesis may submit specimens for Ureaplasma culture and PCR of amniotic fluid only three times. However, specimens from subjects (mothers) and their children who have been found to have new-type coronavirus infection will be discarded and not sent to the "Department of Developmental Medicine, Research Institute, Osaka Women's and Children's Hospital". For details, refer to the Central Assay Specimen Handling Procedures.

At the "Department of Developmental Medicine, Research Institute, Osaka Women's and Children's Hospital", cultures of Ureaplasma spp. and Mycoplasma spp. are conducted, and simultaneous culture and PCR of the bacteria are performed to detect the presence of Ureaplasma urealyticum, Ureaplasma parvum, and Mycoplasma hominis.

#### 7.6 PERIOD OF IMPLEMENTATION AND REGISTRATION

Planned implementation period: jRCT registration date - March 31, 2025

Expected registration period: April 1, 2022 - March 31, 2024

Planned observation period: April 1, 2022 - August 31, 2024

jRCT registration date: February 22, 2022

## **7.7 END OF ENROLLMENT AND OBSERVATION PERIOD**

The registration period will end when the target number of patients enrolled in the study is reached. However, subjects who have already given their consent as study candidates at the time the target number of cases is reached may be enrolled even after the target number of cases is reached. In principle, subjects who have not given their consent at the time the target number of patients is reached can not be enrolled.

The observation period will end when the observation of the last enrolled subject's child is completed.

## **8 METHOD OF OBTAINING CONSENT**

### **8.1 INFORMED CONSENT**

Because we recruit women at or over 18 years old, we should obtain written informed consent solely from patients.

CI, SIs, or CRCs should contact patients, explain the contents of study explanatory document, and obtain written informed consent from patients. CI, SI, or CRCs should explain the content of this trial in words that are easy for the patient to understand, using the explanatory document prepared in accordance with the Clinical Research Act and approved by the Jichi Medical University Central Clinical Research Ethics Committee. CI, SI, or CRCs should give the subjects plenty of time to answer questions and consider their participation in this trial. It also emphasizes that consent is based on the free will of the subject, and that even if they do not agree, they should not be treated disadvantageously. When consent to participate in the study is obtained, the signature, explanation date, and consent date of CI (or SI, CRCs) and subject who made the explanation should be stated on two sets of consent forms (for patients, for institutes). The explanatory document and a consent form for patients should be issued, and a consent form for institutes should be kept at the implementing medical institution. Procedures related to the trial must be carried out after obtaining the consent of the patient for any procedure.

During the trial, if new information is obtained that may affect the will of the study subject, which was not expected at the time of obtaining consent, PI should promptly revise the consent explanatory document, and CI or SI should explain it to the study patient, confirm the intention to participate in the study again, and obtain consent. In addition, in the event of a change in the content of the study, etc., the same should be obtained.

